## Abstract

**Purpose:**

Surgery wait times after diagnosis of appendicitis are an important factor influencing the success of a patient’s treatment. The proposed study will be a quantitative multicenter retrospective cohort design with the primary aim of assessing the difference between appendicectomy wait times between rural and urban hospitals in Western Australia and the effect of this on operative outcomes. Selected outcome measures will be examined by time from initial presentation at an emergency department to the patient being diagnosed and then time of diagnosis to surgery being performed. The secondary aim is to compare rates of negative appendicectomies between hospitals.

**Methods:**

Appendicectomy patients will be identified from operating room register by medical student data collectors; then, each respective hospital’s emergency room data collection will subsequently be accessed to complete case report forms based on demographics and clinical findings, pre-operative investigations, and management and follow-up. Case report forms with > 95% completeness will be accepted for pooled analysis. The expected duration of retrospective data collection will be 8 months. This study RGS6483 has received HREC approval by the Royal Perth Hospital HREC Ethics Committee, with a waiver of consent obtained and the HREC was notified of amendments to the protocol made on April 21, 2024.

Dissemination of results.

Data will be collected and stored online through a secure server running the Research Electronic Data Capture (REDCap) web application. No patient-identifiable data will be entered into the system. Results will subsequently be shared via scientific journal publication and presentation at relevant meetings.

**Supplementary information:**

The online version contains supplementary material available at 10.1007/s00384-024-04662-3.

## Introduction

Surgery wait times after diagnosis of appendicitis are an important factor influencing the success of a patient’s treatment. Clinical evaluation in conjunction with the Alvarado or appendicitis inflammatory response scores is used to determine the risk of appendicitis in symptomatic patients. A large cohort study has shown that, in cases of uncomplicated appendicitis, short delays to operation of < 24 h do not increase the rates of complex appendicitis [1]. This finding was confirmed in a meta-analysis of 11 non-randomized studies, where a short in-hospital delay of 12 to 24 h before surgery did not increase the risk of complex appendicitis including perforation. However, delaying appendicectomy for > 48 h was associated with increased surgical site infections and other complications [2]. A laparoscopic appendicectomy approach should be performed unless contraindicated [3].

Negative appendicectomy refers to surgical removal of the normal appendix on final pathological report [4]. The Second Australian Atlas of Healthcare Variation in 2017 revealed that negative appendicectomy rates in Australia were 21–24% [5]. With appendicectomies carrying many risks such as possible wound infection or rupture, intestinal injury, postoperative abdominal abscess, or urinary infections, unnecessary appendicectomy can have significant impacts [6]. A recent audit conducted to examine pediatric negative appendicectomy rates at Southwest Health Campus Bunbury including 421 patients found the negative appendicectomy rate to be higher than observed in previous literature at 45.58%. The authors noted this was concerning since diagnostic laparoscopy in children is not benign, with negative appendicectomy having a similar morbidity risk to appendicectomy for uncomplicated appendicitis [7].

The proposed study will be a quantitative multicenter retrospective cohort design with the primary aim of assessing the difference between appendicectomy wait times between rural and urban hospitals in Western Australia and the effect of this on selected outcome measures. The secondary aim is to compare the rates of negative appendicectomies between these hospitals.

It is hypothesized that there will be a higher rate of negative appendicectomies in rural hospitals as opposed to metropolitan hospitals, rooting from various potential factors. According to an audit examining the rural–urban differences in surgical interventions in the United States (US), there were higher rates of an array of surgeries including appendicectomies in areas classified rural according to US standards. This was contrary to the authors’ hypothesis that rurally located patients would have lower surgical rates. The authors proposed this could be explained by rural patients experiencing overall poorer health, increasing the indications for many surgeries to be undertaken [8]. This can be extrapolated to the Australian setting, where, according to the Australian Institute of Health and Welfare (AIHW), risk factors such as smoking, obesity, and hypertension amongst many others all increased with rurality, as well as chronic health conditions and burden of disease [9]. Another factor which may contribute to potential higher negative appendicectomies is that doctors may have a lower threshold to perform the surgery in order to avoid potential severe complications, such as perforation in a setting where there is reduced healthcare access. This may in turn lead to reduced surgical wait times in rural settings, addressing both our primary and secondary outcomes. Another US study on pediatric patients revealed that rural hospitals were 50% more likely to perform negative appendicectomies. The authors explained this is due to negative appendicectomies being justified in order to “decrease delay in diagnosis and subsequently lower the risk of appendiceal perforation” [10]. The authors noted that this disparity may also be in part due to reduced access to pre-operative imaging such as computed tomography to make the diagnosis. It is suspected a combination of all stated factors may play a role in reduced surgical wait times and negative appendicectomies in rural compared to metropolitan hospitals in Western Australia.

## Aim

The aim of this study was to determine the variation in appendicectomy surgery wait times between rural and urban areas in Western Australia after initial presentation and diagnosis at an emergency department. Within these populations, selected outcome measures will be examined by time from:Initial presentation for the presenting complaint at an emergency department to the patient being seen by a general surgery registrar or consultant.Time from patient being seen by a general surgery registrar or consultant to surgery being performed.

The reason for taking data based on the two separate time frames is that by recording time between initial emergency department presentation to the patient being seen by the general surgery registrar or consultant, it will be possible to account for those patients who are not immediately diagnosed and then go on to have a delayed diagnostic laparoscopy and appendicectomy and evaluate and measure the magnitude of outcome impacts that an increased duration of this time could produce. Furthermore, the case report forms collect data on previous presentations of the same presenting complaint within the past week to capture any *prior premature discharge from the same site on initial evaluation of presenting complaint*.

This will allow examination of the effect of both triage wait times and timing of surgery after diagnosis on perforation, operation duration, and length of stay amongst each of the subpopulations.

Additionally, it is hoped to establish the rate of negative appendicectomies in urban and rural areas in Western Australia and if necessary make suggestions preoperatively to reduce their incidence.

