### Primary outcome measure

Wait time from presentation (hours) to diagnosis and then surgery. This is the number of hours from initial presentation at an emergency department until review by the surgical team, diagnosis, and then surgery. These parameters will be recorded on the case report forms as date and time and will be used to compare such wait times between rural and metropolitan hospitals.

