## Methods

This protocol adheres to the reporting recommendations relevant specifically to an observational retrospective cohort study of the Guidelines for Reporting Outcomes in Trial Protocols: The SPIRIT-Outcomes (2022), obtained via the Equator Guidelines [12]. Consultation with doctors in the field of general surgery and rural health experts from WACHS was performed in the development of this protocol to ensure that the needs of rural populations are not misrepresented.

The study design was chosen to be retrospective due to the difficulties of prospective recruitment by medical student data collectors for whom it is unrealistic to conduct a prospective study to recruit appendicitis patients due to the transient nature of placements, especially in large metro hospitals, which would likely lead to selection bias (for more details, see “Collaborative teams”). Four separate 2-week data collection periods were preferred over one asynchronous period of data collection to provide structure for the data collection into four 6-month retrospective review periods which would allow more medical students to participate in data collection in the project overall if each student is allocated one data collection period and to divide the amount of retrospective data to be reviewed into a manageable amount for each mini-team (for more details see “Collaborative teams”).

The retrospective time period which will be examined for eligible patients and from which data is collected will be over a 2-year period from January 2022 to November 2023. Appendicectomy patients will be identified from the operating room register by members of the mini-teams discussed in the “Methods” section, expected to be mainly medical student data collectors currently on placement at the relevant hospital, and then, each respective hospital’s emergency room data collection subsequently will be accessed to fill out the case report forms. The data will be collated via case report forms based on demographics and clinical findings, pre-operative investigations, and management and follow-up. Case report forms with > 95% completeness will be accepted for pooled analysis. The expected duration of retrospective data collection will be 8 months. This includes the four 2-week data collection periods.

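### The wait-time intervals are split at diagnosis in one place and at first surgical review in another, so diagnostic delay can be counted as post-diagnosis delay; the clock start for transferred patients is also not stated

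*Protocol article*

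**What the plan says.** All references are to the Protocol article.

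- **Abstract, Purpose.** Outcomes are examined by "time from initial presentation at an emergency department to the patient being diagnosed and then time of diagnosis to surgery being performed". The dividing event is diagnosis.
- **Aim, list of intervals.** The first runs from "Initial presentation for the presenting complaint at an emergency department to the patient being seen by a general surgery registrar or consultant". The second is "Time from patient being seen by a general surgery registrar or consultant to surgery being performed". The dividing event is surgical review.
- **Aim, rationale.** Measuring the first interval is justified because "it will be possible to account for those patients who are not immediately diagnosed", meaning patients who go on to a delayed laparoscopy.
- **Aim, use of the intervals.** The plan will examine "the effect of both triage wait times and timing of surgery after diagnosis on perforation, operation duration, and length of stay". The second interval is here described as starting at diagnosis.
- **Primary outcome measure.** The first sentence divides the wait at diagnosis. The next counts hours "until review by the surgical team, diagnosis, and then surgery", which makes review and diagnosis two successive events. The section adds that these points are recorded on the case report form as date and time.
- **Source of the times.** Under Methods, cases come from the operating room register, and then each hospital's "emergency room data collection subsequently will be accessed to fill out the case report forms". The Aim says earlier visits in the past week are collected to capture "prior premature discharge from the same site". Rural or urban status follows the site. The Criteria section does not mention transfers between hospitals.

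**The concern.** Review and diagnosis are different events, and the text uses them interchangeably as the boundary of the primary wait. This matters because the Aim relates each interval separately to perforation, operation duration and length of stay. If a patient is seen early by the surgical team, observed, and diagnosed late, the Aim's split puts the observation time in the second interval. That interval is then read as delay between diagnosis and theatre. A problem of diagnosis would be reported as a problem of theatre access, in the very patients the first interval was meant to account for.

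The start of the clock raises a related question. The definitions refer only to initial presentation at an emergency department, without saying whose. The data source is the record of the hospital where the operation took place. For a patient who presented elsewhere and was transferred in, the clock may restart on arrival at the second hospital, and the hours at the first would be lost.

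**Working it through.** **Planned numbers.** The Sample size section gives 818 claims in one year, and 2 × 818 = 1,636, consistent with its figure of over 1,600. By site, 4 × 350 = 1,400 urban and 5 × 50 = 250 rural, total 1,650. These serve below only as denominators. The article gives no figure for the delay from review to diagnosis or for the number of transfers, so those inputs are assumed.

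**Step 1: the two definitions applied to one patient.** Illustrative times: presentation 0 h, surgical review 3 h, diagnosis 27 h, surgery 30 h.

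| Split | First interval | Second interval | Total |
|---|---|---|---|
| At diagnosis (Abstract) | 27 h | 30 − 27 = 3 h | 30 h |
| At review (Aim) | 3 h | 30 − 3 = 27 h | 30 h |

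The intervals swap; the total does not change. If review and diagnosis both occur at 27 h, the two splits agree (27 + 3 h), and the Aim's rationale works as written.

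**Step 2: effect on mean intervals.** Let a share q of patients be diagnosed D hours after review. Choosing one split over the other moves q × D hours of mean wait between the intervals.

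| q | D | q × D |
|---|---|---|
| 5% | 6 h | 0.3 h |
| 10% | 12 h | 1.2 h |
| 20% | 12 h | 2.4 h |
| 30% | 24 h | 7.2 h |

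The rural-urban difference in each mean interval changes only as far as q × D differs between the groups. If q × D is equal in both, the shift cancels. If it were 2.4 h in one and 0.3 h in the other, the difference would change by 2.4 − 0.3 = 2.1 h, in opposite directions for the two intervals. The analyses relating each interval to outcomes do not have that protection.

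**Step 3: transfers.** Suppose m patients spend T hours at a rural emergency department and are operated on at an urban site. If the clock starts at the operating site, the urban mean omits m × T / 1,400. If it starts at the first department, those hours are counted in the urban mean. If instead patients were grouped by origin, the rural mean would omit m × T / (250 + m).

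| m | T | Urban mean: m × T / 1,400 | By origin: m × T / (250 + m) |
|---|---|---|---|
| 10 | 12 h | 120 / 1,400 = 0.09 h | 120 / 260 = 0.46 h |
| 50 | 12 h | 600 / 1,400 = 0.43 h | 600 / 300 = 2.0 h |
| 100 | 24 h | 2,400 / 1,400 = 1.71 h | 2,400 / 350 = 6.86 h |

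These rows show how the size depends on m and T. They are not estimates for this study.

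**The case against.** The best defence is that the split is an error of labelling, not of data. Primary outcome measure says the times are recorded, so any interval can be derived later, and total presentation-to-surgery time is the same under either definition. The 12 h standard under Audit standards for outcome measures refers to that total. All of this stands, and it is why the correction is cheap. It does not remove the contradiction: an analyst following the Aim and one following the Abstract would report different intervals under the same description.

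Several stronger readings are tempting, but the article does not support them.

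- **That the review split fails for everyone not diagnosed at once.** It fails only for those reviewed early and diagnosed late. If the surgical review was itself late, the delay falls in the first interval as intended. The shares are not given.
- **That the clock starts at the operating hospital.** This is a reasonable inference from the data source and the same-site wording, but no rule says so. The case report form is not shown and may define the times or record transfers.
- **That transferred rural patients end up in the wrong arm.** This presumes grouping by patient origin. The Introduction and Primary outcome measure compare hospitals, and Methods classifies by site, so a patient operated on at an urban hospital belongs in the urban group. The Aim does speak of areas, which calls for clarification but does not show misclassification.
- **That the significance level is attached to the wrong comparison.** Data analysis mentions 0.05 only for wait time against complications. How it applies to the primary comparison may be left to an analysis plan that is not shown.

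**Conclusion.** The point holds for the split. The Abstract, the Aim and Primary outcome measure do not agree on the event that divides the primary wait. Under the Aim's version, diagnostic delay after an early review is counted and interpreted as delay after diagnosis, contrary to the stated rationale for those patients. The shift is q × D hours in each mean interval, 0.3 to 7.2 h over the assumed range, with no effect on the total. The contradiction itself rests on the text and needs no assumption; only its size does.

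The transfer point holds as a possible bias of unknown size. It depends on whether transfers occur in number, how long those patients waited before transfer, and whether the unseen form already deals with them.

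**What to change.** 1. Make hours from initial emergency department presentation to surgery the single primary outcome. It does not depend on the disputed boundary and matches the interval in the article's own 12 h audit standard.
2. Report presentation to surgical review, review to diagnosis, and diagnosis to surgery as separate secondary intervals, from the date-times that are to be recorded.
3. Use the same labels in the Abstract, Aim and Primary outcome measure, and correct the Aim's rationale: late diagnosis after an early review appears in review-to-diagnosis, late review in presentation-to-review.
4. State which emergency department starts the clock for a patient transferred in. If the case report form does not already do so, add a transferred-in item with the referring site and the arrival time there.
5. Add a sensitivity analysis that leaves transfers-in out or assigns them to the hospital of first presentation.

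Items 1 to 3 cost only wording. Items 4 and 5 cost a few form fields, and some referring-site times will be missing because the source is each hospital's own record. The form fields are best settled before extraction, since adding them later means reopening records.

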### Data analysis

Normally distributed data will be reported as mean (standard deviation (SD)), and non-normally distributed data will be reported as median (interquartile range (IQR)). Independent *t*-tests or ANOVAs will be used for normally distributed variables, Mann–Whitney *U* and Kruskal–Wallis tests will be used for non-normally distributed continuous or ordinal variables, and chi-squared tests will be used for categorical variable comparisons. When comparing appendicectomy wait times with complication incidence during the data analysis phase, a *P* value of 0.05 will be used to determine statistical significance. There will be no interim analysis or audit planned due to the grouping of data sets over four data collection periods. As this is a retrospective observational cohort study, there are no plans to deviate from the original protocol statistical plan or study design.

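### The listed tests cannot separate the effects of the two wait intervals on outcome; if the intervals are correlated, an effect of one can appear as an effect of the other

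*Protocol article*

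**What the plan says.** The Aim section defines two intervals. The first is "Initial presentation for the presenting complaint at an emergency department to the patient being seen by a general surgery registrar or consultant". The second is "Time from patient being seen by a general surgery registrar or consultant to surgery being performed". It states that "selected outcome measures will be examined by time from" each of these. The passage opening "The reason for taking data based on the two separate time frames" explains that recording the first interval accounts for patients who are not diagnosed straight away, and allows the authors to "evaluate and measure the magnitude of outcome impacts that an increased duration of this time could produce". It continues: "This will allow examination of the effect of both triage wait times and timing of surgery after diagnosis on perforation, operation duration, and length of" (the sentence ends with hospital stay, and applies within each of the subpopulations).

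The Data analysis section then names the methods. T-"tests or ANOVAs will be used for normally distributed variables", Mann–Whitney and Kruskal–Wallis tests for non-normal or ordinal variables, and "chi-squared tests will be used for categorical variable comparisons". The significance threshold is 0.05. The section adds that no departure from the statistical plan is intended. No regression or other model with more than one explanatory variable is mentioned.

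The Hospital stay length section counts stay in days from the date of presentation to the emergency department.

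**The concern.** The aim is attribution: how much a longer wait before surgical review affects outcome, and how much a longer wait after it does. The listed methods are comparisons between groups. Used as listed, they relate each interval to each outcome separately.

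Both intervals belong to the same patient and may share causes such as the hospital or an uncertain diagnosis. If they are correlated, an interval with no effect of its own will still be associated with outcome through the other. With a negative correlation the spurious association has the opposite sign. Balancing the groups for disease severity would not remove this.

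The practical stake is that delay in the emergency department and delay in reaching theatre point to different service changes, and a report could name the wrong one. In addition, Mann–Whitney and chi-squared tests do not by themselves give the magnitude of impact that the aim promises.

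**Working it through.** **Inputs from the protocol article.** The Sample size section gives 818 claims in a year, doubled: 2 × 818 = 1636. It also gives 4 metropolitan hospitals at 350 and 5 rural hospitals at 50: 1400 + 250 = 1650. Both agree with its figure of over 1600. Alpha is 0.05, taken as two-sided because sidedness is not stated. No power, effect size or between-interval correlation is given.

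**Assumptions not in the documents.** One interval affects outcome, with expected z = 4 in the whole cohort. The other has no effect. The correlation rho between them ranges from 0 to 0.5.

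**Formula.** Tested alone, the null interval has expected z of rho × z. Its chance of significance is P(Z > 1.96 − rho·z) + P(Z < −1.96 − rho·z).

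**Scaling to the subgroups.** The aim refers to subpopulations, so z is scaled by the square root of n.
- Urban: 4 × √(1400/1650) = 3.68
- Rural: 4 × √(250/1650) = 1.56

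| rho | All, rho × 4 | All, n = 1650 | Urban, n = 1400 | Rural, n = 250 |
|---|---|---|---|---|
| 0 | 0 | 5% | 5% | 5% |
| 0.2 | 0.8 | 13% | 11% | 6% |
| 0.3 | 1.2 | 22% | 20% | 7.5% |
| 0.5 | 2.0 | 52% | 45% | 12% |

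The rates are the same for negative rho, with the false effect reversed in sign. In 2000 simulated cohorts of 1650, the null interval was significant alone in 21.7% at rho 0.3 and 51.5% at rho 0.5. With both intervals in one model the rates were 4.8% and 5.2%.

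**What z = 4 means.** For a binary outcome with an assumed 25% risk, the standard error of the log odds ratio per SD is about 1/√(1650 × 0.25 × 0.75) = 1/17.6. So z = 4 corresponds to a log odds ratio of 0.227, or an odds ratio of about 1.26 per SD of the interval.

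**Check with a listed test.** A second simulation (1000 replicates per setting, n = 1650, 25% risk) gave the first interval a real effect and the second none. The second was compared between outcome groups by Mann–Whitney test.

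| rho | True odds ratio 1.3 per SD | True odds ratio 1.5 per SD |
|---|---|---|
| 0 | 4.9% | 4.7% |
| 0.1 | 6.5% | 10.8% |
| 0.2 | 14.7% | 26.1% |
| 0.3 | 27.9% | 53.7% |
| 0.5 | 59.5% | 93.6% |
| −0.3 | 25.5% | 52.6% |

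In the odds ratio 1.5 case, the null interval's apparent odds ratio was 1.13 at rho 0.3, 1.22 at 0.5 and 0.89 at −0.3. With both intervals in one logistic model, it was significant in 4 to 7% of replicates, with a mean odds ratio of 0.997 to 1.003. With 250 rural patients and odds ratio 1.5, the single-interval rates were 12.3% at rho 0.3 and 26.2% at 0.5.

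**The case against.** **Covariate models may sit in a fuller plan.** The article is condensed, and ANOVA need not be one-way. That the intervals will be tested one at a time is an inference from the test list. However, the section names its tests and says the plan will not change. A two-factor ANOVA would not serve perforation, which is binary. The mismatch is between a stated aim and a stated method, so this objection softens the wording but does not remove the point.

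**The first interval's unadjusted association may be what is wanted.** It comes first. If late review pushes surgery later, the second interval is a mediator, and part of the first interval's crude association is a real effect. This stands. The rates above are error rates for the first interval only if none of the correlation is causal. Adjusting the second interval for the first is uncontroversial. Adjusting the first for the second gives only its direct effect.

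**Correlation is assumed.** This also stands. The article gives none, and at rho = 0 there is no misattribution.

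**Stronger readings that the documents do not support.** A reader might infer that an effect of one interval will necessarily be credited to the other; that requires correlation, which is unknown. A reader might infer that splitting the wait has lost its purpose. It has not: recording the intervals separately still describes each, identifies late surgical review, and supports the rural–urban comparison that is the primary outcome. A reader might also infer that a negative correlation would hide a real effect. That needs both intervals to matter, and no figure here shows it.

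**Conclusion.** The point holds in conditional form. The article promises the effect of each interval on perforation, operation duration and stay, and the tests it lists cannot separate the two. At z = 4 for the real interval in the whole cohort, the false-positive rate for a null interval runs from the nominal 5% to about half of studies as rho goes from 0 to 0.5. It is smaller in the rural group alone. Both the z value and the range of rho are assumptions. The primary rural–urban comparison of wait times is not affected. What is at risk is attributing an outcome effect to one interval. This should be corrected before analysis.

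Length of stay is a separate difficulty: counted from presentation, it contains both intervals by definition, so positive associations are built in and joint modelling alone does not remove them.

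**What to change.** In the Data analysis section, state the following.

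- Each outcome is regressed on both intervals together, accounting for hospital, within the rural and urban groups: logistic regression for perforation or complex appendicitis, and linear regression on a suitable scale for operation duration.
- Each interval's effect is reported per hour with a 95% confidence interval, together with the correlation between the intervals.
- The first interval's effect is also reported without the second in the model, as its total effect, because the second may mediate it.
- For this analysis, length of stay is counted from surgery.

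The cost is a change of wording and a little more analysis; the dates and times that define the intervals are already to be recorded on the case report forms. Confidence intervals widen somewhat if the waits are strongly correlated. In the linear case the standard error grows by a factor of about 1/√(1 − rho²), which is 1.05 at rho 0.3 and 1.15 at 0.5. The joint model removes confounding of each interval by the other, but not confounding by severity or other case mix.

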## Audit standards for outcome measures

The optimal timing of appendicectomy for uncomplicated acute appendicitis should be within 12 h of initial presentation at an emergency department [1].

Laparoscopic appendicectomy approach should be performed unless contraindicated [3].

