### Criteria

Inclusion criteria:(i)All patients who undergo an appendicectomy during the study period.(ii)Age 16 years or older at time of presentation

Exclusion criteria:(i)Previous appendicectomy or right hemi-colectomy or total colectomy.(ii)Current pregnancy at time of presentation

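### Patients with a normal appendix are left in the perforation analyses, so the rural–urban comparison of perforation is biased under the study's own hypothesis

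*Protocol article*

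**What the plan says.** **Cohort.** Protocol article, Criteria: "All patients who undergo an appendicectomy during the study period", aged 16 or older. The exclusions are earlier removal of the appendix or relevant colon and "Current pregnancy at time of presentation". A normal appendix is not an exclusion. The section on the rate of negative appendicectomy keeps it as one of three recorded categories (normal, simple, complex).

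**Timing analysis.** Aim: the study will examine the "effect of both triage wait times and timing of surgery after diagnosis on perforation", and the sentence goes on "on perforation, operation duration, and length of stay amongst each of the subpopulations". The analysis of waits is therefore described within rural and within urban patients.

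**Between-setting aim.** Introduction: the primary aim is the difference in waits "between rural and urban hospitals in Western Australia and the effect of this on selected outcome measures". Perforation is among the outcomes that the Aim lists.

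**Hypothesis.** Introduction: "It is hypothesized that there will be a higher rate of negative appendicectomies in rural hospitals as opposed to metropolitan hospitals". One suggested cause is a lower threshold to operate, and "This may in turn lead to reduced surgical wait times in rural settings, addressing both our primary and secondary outcomes".

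**Standard.** Audit standards: "The optimal timing of appendicectomy for uncomplicated acute appendicitis should be within 12 h of initial presentation". The benchmark concerns patients who have appendicitis.

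No section names confirmed appendicitis as the population for perforation. Data analysis lists only unadjusted group comparisons.

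**The concern.** Perforation is a complication of appendicitis. A patient whose appendix is normal on final pathology is not at risk of it, whatever the wait. If such patients stay in the denominator, the perforation rate per appendicectomy is the product of two quantities: the share of patients who truly have appendicitis, and the perforation risk among them. Only the second can respond to waiting.

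The study expects the first quantity to differ between rural and urban hospitals, and expects waits to differ too. A lower rural perforation rate could then be credited to shorter rural waits when it only reflects more normal appendices. The finding on negative appendicectomy would leak into the finding on delay. This is distinct from confounding by severity: it would remain even if operating priority took no account of how ill the patient was.

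**Working it through.** **1. The plan's own figure.** Sample size projects over 1600 participants. Doubling the annual claims gives 2 × 818 = 1636. Summing the sites gives 4 × 350 + 5 × 50 = 1400 urban + 250 rural = 1650. Both agree with the stated figure. Rural patients are 250/1650 = 15%.

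**2. Inputs.**
- Urban negative rate: 22.5%, the midpoint of the national 21–24% cited in the Introduction.
- Rural negative rate: 1.5 × 22.5% = 33.75%, reading the US paediatric finding of 50% more likely as a risk ratio. Upper case: 45.58%, from the paediatric audit at Bunbury.
- Perforation among true appendicitis, q: not given. Assumed 20%, range 15–35%, the same in both settings and unrelated to wait.

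**3. Rural against urban, all appendicectomies.** Perforation rate = q × (1 − negative rate).
- Urban: 0.20 × 0.775 = 15.5%.
- Rural, base case: 0.20 × 0.6625 = 13.25%. Odds ratio, urban v rural = (0.155/0.845) / (0.1325/0.8675) = 1.20.
- Rural, upper case: 0.20 × 0.5442 = 10.9%. Odds ratio 1.50.

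The rural/urban risk ratio does not depend on q: 0.6625/0.775 = 0.85, or 0.5442/0.775 = 0.70 in the upper case. For q from 15% to 35% the odds ratio runs from 1.19 to 1.23, or from 1.48 to 1.58.

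**4. Would the planned sample show it?** With 1400 v 250, the expected rates give P = 0.36 in the base case and P = 0.058 in the upper case. Over urban negative rates of 21–24% and q of 15–35%, the chance of a false P < 0.05 (two-sided, assumed) is 10–28% with the ratio of 1.5, and 31–83% with 45.58%.

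**5. Wait against perforation, settings pooled.** Take the extreme in which all 250 rural patients fall in the short-wait half of 825. Negatives there are (250 × 0.3375 + 575 × 0.225)/825 = 25.9%, against 22.5% in the long-wait half. With q = 20% the odds ratio is 1.05. With 45.58% the short-wait half has 29.5% negatives and the odds ratio is 1.12.

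**6. Simulation with no effect of waiting.** 2000 runs of 1400 urban and 250 rural patients; 22% urban negatives; q = 25%. Rural negatives are 33% or 45.58% in the first row and 33% in the others. Rural waits are shorter by 0.5 or 1.0 SD in the first row, and by 0 or 0.5 SD in the others. The test is Mann–Whitney on wait by perforation; odds ratios are for long v short wait, split at the median. All shifts are assumptions.

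| Waits of patients with a normal appendix | Pooled OR (false rejection) | Urban only OR (false rejection) |
|---|---|---|
| Same as others in their setting | 1.02–1.08 (5–12%) | 1.00 (4–6%) |
| 0.25 SD shorter | 1.12–1.14 (21–26%) | 1.12 (17–18%) |
| 0.5 SD shorter | 1.26–1.27 (62–67%) | 1.24 (48–50%) |
| 0.25 SD longer | 0.90–0.91 (15–19%) | 0.90 (15–16%) |
| 0.5 SD longer | 0.79–0.81 (54–62%) | 0.80–0.81 (49–51%) |

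In the first row, rejection within rural is also 4–6%. Restricted to confirmed appendicitis, every scenario returns an odds ratio of 1.00 and 4–6% rejection.

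**The case against.** A reader might infer that the hypothesis of shorter rural waits and more rural negatives by itself creates an association between waiting and perforation in the analysis the Aim describes. It does not. That analysis is set within each subpopulation, and a difference between settings cannot produce an association inside one of them. Even if the settings were pooled, step 5 shows an odds ratio of at most about 1.05–1.12, because so few patients are rural. One can obtain a striking result by assuming 35% negatives among short waits and 10% among long ones (13% v 18% perforation at q = 20%; P = 0.006 with 800 per half). Rural–urban status cannot generate a gap of 25 percentage points; step 5 gives 3.4 to 7.0.

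Nor is the direction within a setting fixed. A lower threshold to operate suggests that patients with a normal appendix wait less. The Aim's own account of undiagnosed patients who come late to diagnostic laparoscopy suggests that some wait longer.

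Three further points stand. Both rural inputs are paediatric, while this study takes age 16 and over. The definition of complex appendicitis can already be read as a rate among appendicitis cases, so its denominator is unclear rather than wrong. And patients with a normal appendix do have an operation duration, a hospital stay and possible complications, so there is no reason to drop them from those outcomes.

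It can also be said that denominators belong in an analysis plan that is not shown. That has some force, but the article itself fixes the cohort, names perforation as an outcome and predicts the imbalance that makes the combination misleading.

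**Conclusion.** The concern holds for the between-setting comparison. As written, more than a fifth of the perforation denominator (cited 21–24%) cannot have the event. Under the study's hypothesis, rural sites would show less perforation with no effect of waiting: 13.25% against 15.5%, odds ratio 1.20, rising to 1.50 in the upper case. The odds ratios rest on an assumed 20% perforation rate and on paediatric rural figures; the risk ratios of 0.85 and 0.70 rest only on the negative rates.

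For waiting against perforation within a setting, the rural–urban mechanism contributes nothing. A bias arises there only if patients with a normal appendix wait differently from true cases, which the document neither establishes nor rules out, and it could go either way. Stratifying by setting does not remove that possibility; restricting to confirmed appendicitis does. This is a cheap improvement to make before analysis, not a must-fix.

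**What to change.** In Aim and in the definition of the rate of complex appendicitis, state that perforation and complex appendicitis, both by wait and rural against urban, are analysed among patients with appendicitis on the final pathology report, with the rural and urban strata kept.

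Keep all eligible appendicectomies for the negative rate, the wait comparison, operation duration, stay and complications. If wanted, repeat the last three in confirmed appendicitis as a sensitivity analysis.

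The cost is one sentence in each place and a denominator about 20–25% smaller for perforation and complex appendicitis (base case: (1400 × 0.225 + 250 × 0.3375)/1650 = 24%). No event is lost, and no new data are needed because the case report form already records normal, simple or complex.
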